## Introduction

### Rationale

Alzheimer's disease (AD) is a progressive disease affecting brain function and independent living and eventually requires full-time care. There are only a few treatments that temporarily help symptoms such as memory loss; however, these eventually become ineffective as the underlying disease progresses unabated. Part of the difficulty of treating AD is that it involves the activation of many destructive processes in the brain, each of which is likely to need simultaneous treatment if the progression of the disease is to be halted.

For this reason, there is urgent need for new evidence about medications that could influence the incidence and progression of AD. One promising approach is to investigate drug repositioning,^1^ which offers a time-effective and cost-effective alternative to traditional drug development. A recent consensus study of dementia experts identified a short-list of individual and classes of prescribed drugs that may be repurposed as novel treatments for dementia.^2^ The short-list included compounds used to treat hypertension, hypercholesterolaemia and type 2 diabetes, all of which can be classed as having ‘cerebroprotective’ properties and have variable levels of preclinical evidence that suggest they may have beneficial effects for various aspects of dementia pathology. However as yet there is limited pharmacoepidemiological data to support their effects in human populations. Therefore, we plan to investigate whether these existing medications could be repurposed to prevent or treat AD.

Furthermore, the overlap of different forms of neurodegenerative disease would suggest that there may be scope to translate existing or newly identified interventions for testing in neurodegenerative diseases where similarities exist. Thus, we will start by examining the most common form of neurodegenerative disease—AD.^3^
^4^ We will then investigate whether the drug candidates could also be repurposed to treat or prevent other neurodegenerative diseases—these will include other non-Alzheimer's disease dementias (NADD) (ie, the group for dementias in which AD is not thought to play a part), Parkinson's disease (PD) and amyotrophic lateral sclerosis (ALS). Collectively, these findings will allow the prioritisation of drugs to be tested as repurposed treatments in clinical trials of AD and other neurodegenerative diseases in the future.

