#### Cohort A

For each treatment, we will create a cohort of patients who are diagnosed with the condition the treatment is used for or ‘at risk’ of that condition. This will be determined by the indications and test results described in table 2. We will split each cohort into ‘exposed’ and ‘unexposed’ groups. The ‘exposed’ group will consist of patients who received a treatment of interest within 6 months of initial diagnosis of the condition for which the treatment is being given (the ‘indication’ for treatment). The ‘unexposed’ group will consist of all others in the cohort. Patients will be identified as having received a treatment of interest by product codes (see online supplementary files 1–3). Therefore, in this analysis, we will compare an ‘exposed’ group of individuals who were prescribed the treatment to an ‘unexposed’ group of individuals who received similar test results (ie, were ‘at risk’ of or diagnosed with the indication for treatment), but did not receive the treatment, as illustrated in figure 1. The aim of this approach is to address confounding by indication that could cause bias if the ‘unexposed’ group is drawn from the full population, whom are likely to be healthier. It will also allow us to minimise excluded immortal time bias as patients will be followed from a consistent index date (date first at risk or date of first diagnosis of the condition itself if there was no preceding period at risk).

**Table 2 BMJOPEN2016012044TB2:** The cohorts of type A, one for each treatment of interest

Cohort	Entry criteria
Treatments for hypertension	Patients who are ‘at risk’ of hypertension as indicated by one of the following: Medical code indicating a diagnosis of ‘at risk’ of hypertension. Recorded systolic blood pressure test result between 120 and 139 mm Hg. Recorded diastolic blood pressure test result between 80 and 89 mm Hg. In the case of no period ‘at risk’, patients who have hypertension as indicated by one of the following: Medical code indicating a diagnosis of hypertension. Product code indicating treatment for hypertension. Recorded systolic blood pressure test result of 140 mm Hg or more. Recorded diastolic blood pressure test result of 90 mm Hg or more. See online supplementary file 1 for code lists relating to hypertension.

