**Figure 1 BMJOPEN2016012044F1:**
[figure not shown]
The cohort construction for cohort type A, designed to eliminate immortal time bias. A patient will enter the cohort for a given treatment when they first become ‘at risk’ of the condition the treatment is used for or, in the case of no period ‘at risk’, when they are first diagnosed with the condition (see table 2). For example, when they are diagnosed as at ‘at risk of’ hypertension or, in the case of no period ‘at risk’, when they receive a diagnosis of hypertension. We define cohort entry in this way to avoid excluded immortal time bias that can occur when cohort entry is determined by treatment variation over time.^33^
^34^ Immortal time is the period during follow-up when the outcome cannot occur. Consider the hypertension example above, suppose we started following the treated patients in our cohort from the date of their first prescription of a treatment for hypertension and the untreated patients from a matched date. This would make it impossible for the treated patients to have an outcome, such as dementia, prior to their first prescription. Consequently, patients in this group would all have a period before treatment, when they could not be diagnosed with dementia, that is, they could not experience the outcome. This period is their immortal time, and it must be correctly attributed to the ‘unexposed’ group so that their outcome is not falsely attributed to their exposure. To do this, patients in the ‘exposed’ and ‘unexposed’ groups must be followed-up and compared from the same start date. In this cohort, we are minimising excluded immortal time by following patients from either a test result or diagnosis where possible. In order to capture all relevant patients, we will allow those receiving treatment without a recorded diagnosis to be included as it is assumed treatment suggests a diagnosis.

10.1136/bmjopen-2016-012044.supp1supplementary file

10.1136/bmjopen-2016-012044.supp2supplementary file

10.1136/bmjopen-2016-012044.supp3supplementary file

Follow-up for cohort A will start on the first date a patient is diagnosed with the condition the treatment is used for or ‘at risk’ of that condition (see table 2 and online supplementary files 1–3.) Follow-up will end with the earliest of a relevant neurodegenerative disease diagnosis, death or censoring due to the end of registration at a CPRD general practice.

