#### Cohort B

In this analysis, we will compare different drug subclasses that exist for a given treatment (listed in box 1). To do this, we will create a cohort of all patients who were prescribed a treatment and categorise them by the drug subclass they initially received. This will allow us to compare the outcomes for each of the resulting subgroups. For each treatment, we have defined the most frequently prescribed subclass as the control (indicated in box 1). In the primary analysis of this cohort, we will exclude patients initially prescribed the control subclass if they receive another subclass of the same treatment at the same time, however we do not expect this to be a common. We will explore the outcomes of individuals prescribed multiple subclasses, other than that specified above, in a sensitivity analysis.
Box 1The drug subclasses of interest for each treatment group with the control treatments indicatedTreatments for hypertensionBeta-adrenoceptor blocking drugs (control)Angiotensin-converting enzyme inhibitorsThiazides and related diureticsCalcium channel blockersLoop diureticsAlpha-adrenoceptor blocking drugsCentrally acting antihypertensive drugsAngiotensin-II receptor antagonistsVasodilator antihypertensive drugsPotassium-sparing diuretics and aldosterone antagonistsTreatments for hypercholesterolaemiaStatins (control)FibratesBile acid sequestrantsOmega-3 fatty acid compoundsEzetimibeNicotinic acid groupTreatments for type 2 diabetesBiguanides (control)SulphonylureasOther antidiabetic drugs

Follow-up for cohort B will start on the date of first eligible prescription as determined by a product code (see the treatment code lists in online supplementary files 1–3). Follow-up will end with the earliest of a relevant neurodegenerative disease diagnosis, death or censoring due to the end of registration at a CPRD general practice.

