#### Outcomes

For incidence, we will identify the neurodegenerative disease outcomes (AD, NADD, PD and ALS) by the first record of a relevant read code (see online supplementary file 4) or the first record of a product code indicating treatment for the neurodegenerative disease (see online supplementary file 5). For incidence and progression, we will identify deaths using linked Office of National Statistics (ONS) data.

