### Bias

There are three main sources of bias in our results: ascertainment bias, collider bias and immortal time bias. To overcome ascertainment bias, we will control for consultation rate in our analyses because people who have more chronic conditions such as hypertension, diabetes or renal insufficiency may have higher rates of consultation, which may also increase the opportunity for recording other diagnoses such as dementia. Collider bias could occur if we conditioned on events that happened as a result of the prescription the patient was issued. To prevent this form of bias from affecting our results, we will define each covariate using data inputted prior to the index date.^14^ Finally, we will minimise the risk of immortal time bias in two ways. First, to prevent misclassified immortal time, we will define exposures based on the first prescription observed in the database^10^ and use an intention-to-treat analysis. Second, to minimise immortal time, we will follow-up patients (exposed and unexposed) from a consistent index date. This will be a test result or a read code indicating diagnosis where possible;^15^ however, to capture all relevant patients, we will allow those receiving treatment without a recorded diagnosis to be included.

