#### Instrumental variable analysis

In our third analysis, we will estimate the effects: (1) treatment or no treatment and (2) the specific subclass of medication prescribed, using physicians' prescribing preferences as instruments for the prescriptions the GPs issue to their patients. We cannot directly measure the physicians' preferences; therefore, we will use the prescriptions they issued to their previous patients as a proxy for their preferences. For example, if the instrument were based on just one previous prescription, physicians who previously prescribed the treatment therapy would be categorised as a ‘treatment prescriber’ otherwise they would be categorised as a ‘control prescriber’. As with our previous studies we will use seven prior prescriptions to improve the strength of the instruments.^25–27^ Using multiple prior prescriptions will maximise power. We will report risk differences in the outcomes using additive structural mean models estimated via the generalised method of moments.^28–30^ We will categorise each of the adverse event outcomes as occurring within 3, 6, 9, 12, 24 and 48 months of index date. Methods for estimating survival models using instrumental variables are not well developed. Therefore, we will explore potential instrumental variable survival models in a secondary analysis.^31^

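### Cohorts A and B count diagnoses from the index date with no lag, so neurodegenerative disease already developing when a drug or subclass was chosen enters the incidence hazard ratios

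*Protocol article*

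**What the plan says.** All references are to the protocol article.

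- **Start of follow-up, cohort B** (Cohort B): "Follow-up for cohort B will start on the date of first eligible prescription as determined by a product code".
- **Start of follow-up, cohort A** (Cohort A, text after Figure 1): "Follow-up for cohort A will start on the first date a patient is diagnosed with the condition the treatment is used for", or is at risk of it. Exposed patients are "patients who received a treatment of interest within 6 months of initial diagnosis of the condition", so treatment can begin after the index date.
- **End of follow-up, both cohorts:** "Follow-up will end with the earliest of a relevant neurodegenerative disease diagnosis, death or censoring due to the end of registration".
- **Outcome** (Outcomes): incidence is identified "by the first record of a relevant read code", or by a first product code for treatment of the disease. No minimum time from index is set.
- **Instrumental variable analysis:** "We will categorise each of the adverse event outcomes as occurring within 3, 6, 9, 12, 24 and 48 months of index date". Every window opens at the index date.
- **Bias:** "There are three main sources of bias in our results: ascertainment bias, collider bias and immortal time bias". The Confounding section adds confounding by indication and time-dependent confounding. Neither section names reverse causation.
- **Sensitivity analyses named:** accuracy of outcome coding (Strengths and limitations), patients on several subclasses (Cohort B) and imputation (Missing data). None delays the counting of outcomes.

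**The concern.** The incidence cohorts ask whether a drug prevents disease. The Rationale says that "Alzheimer's disease (AD) is a progressive disease affecting brain function and independent living", and such a disease may be present for some time before it is coded. A patient whose dementia or PD is coded a few weeks after a first prescription very probably had it when the prescriber made the choice. That event says something about who receives which drug, or when disease is noticed, and nothing about prevention.

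The mechanism differs between the cohorts:

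- **Cohort B.** Everyone starts a drug at index. The issue is whether people with early, unrecognised disease are steered towards one subclass rather than another.
- **Cohort A.** Two further routes exist. People in decline may be treated less or more readily than others, and starting treatment may bring contacts at which disease is found. The first can look like protection or harm; the second looks like harm.

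At stake is the use that the Rationale gives to the results: choosing drugs to take forward into clinical trials.

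**Working it through.** **1. Is there a lag anywhere?** The sections on cohorts, exposures, outcomes, bias, confounding, missing data and the four methods contain none. The 12-month rules (Participants, Table 1, Exposures) look back from the start of follow-up, at records and prior drug use. They do not postpone outcome counting.

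**2. Does another stated element do the same job?**

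| Element | What it does | What it leaves |
|---|---|---|
| Consultation rate (Covariates, Bias) | Adjusts for visits before index | Contacts generated by starting treatment |
| Pre-index covariates, propensity score | Balance recorded history | Disease not yet recorded |
| Marginal structural models | Handle measured time-dependent confounding; Statistical methods concedes the assumption of no unmeasured confounders | Undiagnosed disease |
| Instrumental variables | May reduce selection by undiagnosed disease | Detection caused by treatment; early events remain in every window |
| Proportional-hazards test | May flag an effect confined to early follow-up | The early events stay in the estimate |

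**3. Scale, for illustration only.** The document gives neither the share of events in an early window nor the hazard ratio there, and it states no size for this bias that could be reproduced. Let f be the share of events in the affected window, h the hazard ratio there, and let the true later hazard ratio be 1. Approximately,

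overall HR = exp(f × ln h), so the h that alone produces a given overall HR is exp(ln(HR)/f).

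The detectable HRs for cohort B in Table 3 serve only as markers of what the study regards as a detectable effect. Each refers to the smallest exposed subclass against control.

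| Treatment group (Table 3 HR) | f = 5% | f = 10% | f = 20% | f = 30% |
|---|---|---|---|---|
| Hypertension (0.968) | 0.52 | 0.72 | 0.85 | 0.90 |
| Type 2 diabetes (0.943) | 0.31 | 0.56 | 0.75 | 0.82 |
| Hypercholesterolaemia (0.844) | 0.03 | 0.18 | 0.43 | 0.57 |

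Example: ln 0.968 = −0.0325; −0.0325/0.10 = −0.325; exp(−0.325) = 0.72.

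Other direction: h = 1.5 and f = 20% give exp(0.2 × ln 1.5) = exp(0.0811) = 1.084.

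**4. How fragile is this?** Suppose the affected window is the first of 10 years and h = 0.7.

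- Constant event rate: f = 1/10, overall HR = exp(0.10 × ln 0.7) = 0.965.
- Event rate rising 10% a year: f = 1/(1 + 1.1 + … + 1.1⁹) = 1/15.94 = 6.3%, overall HR = exp(0.063 × ln 0.7) = 0.978.

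The two answers fall on either side of 0.968. A modest early distortion can therefore matter for hypertension, but whether it does cannot be settled from the document.

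**The case against.** The strongest reply has four parts.

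- **The plan already contains relevant tools.** Undiagnosed disease that influences prescribing is unmeasured confounding. The Covariates section expects instrumental variables to account for that to some degree, and Table 1 assigns them to cohorts A and B. An early-only artefact is also a departure from proportional hazards, which the plan will test, and the 3- to 48-month windows give some view of timing. This stands as mitigation. It does not take early events out of the Cox, propensity-matched or marginal structural estimates, and the windows are cumulative from index.
- **The mechanisms are not equal across cohorts.** Holding back treatment and detection on starting treatment are contrasts of treated with untreated, hence mainly cohort A. Table 3 gives no detectable HR for cohort A. This stands, and it limits the cohort B concern to choice of subclass.
- **A lag can itself do harm.** In cohort A, unexposed patients have no prescription date. Starting treated patients at prescription and untreated ones at a matched date is the design that the Figure 1 text rejects. Dropping people who die or leave during the lag also conditions on events after prescription, and it moves away from the trial-like target of the primary analysis. This stands, and it argues for a lagged sensitivity analysis rather than a replacement primary.
- **An article may leave sensitivity analyses to a fuller plan, and a list of main biases need not be exhaustive.** This is partly right. But the article itself fixes when counting starts and ends and sets out the biases it intends to handle, so the point concerns stated design.

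A reader might go further and infer that the bias favours the drugs, or that most small protective effects in cohort B would be artefacts. The document supports neither: it gives no early hazard ratio, event timing or length of follow-up, and the direction is open.

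**Conclusion.** The point holds in a limited form. As written, the incidence analyses include diagnoses made straight after the index date, no stated element removes them, and reverse causation is not among the biases or confounding sources named. The size and direction of the resulting bias are unknown. The figures above rest on an assumed early event share, an assumed early hazard ratio, a null later effect and a log-average approximation to the Cox estimate. Under those assumptions, the hypertension comparison is the most exposed and hypercholesterolaemia much the least. A large sample does not help, because it narrows the interval without moving the bias. This is an improvement worth making before analysis; it does not show that the design fails.

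**What to change.** 1. **Cohort B.** Prespecify sensitivity analyses that begin counting outcomes and person-time 12 and 24 months after the first prescription, identically in all subclasses. Report them beside the unlagged primary estimate. State in advance that an association which disappears after the lag will not be read as support for prevention.
2. **Cohort A.** Apply a lag without creating immortal time. One way is to treat exposure as time-varying, with the lag running from first prescription. Another is a common landmark, set after exposure has been classified and identical in both groups.
3. **Bias section.** Name reverse causation, and say that the pre-index consultation rate does not cover contact arising from the start of treatment.

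**Cost.** For cohort B, the same models rerun on data already held; cohort A also needs its exposure or landmark coding set up. Events and patients from the lag period are lost, so precision falls somewhat, and the lagged estimate applies to people still event-free and under follow-up when the lag ends. A lag reduces this bias but may not eliminate it if the undiagnosed phase is longer than the lag.

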#### Covariates

We will match all covariates on date of birth, sex, year of index date and years of recorded history in the database before the index date. The covariates we will include in our analyses are body mass index, smoking status, alcohol consumption, a postcode-based measure of socioeconomic position, previous history of coronary-artery disease, previous coronary-bypass surgery and cerebrovascular disease including stroke. We will also control for other major chronic illness (including cancer, arthritis) using the Charlson Index^11^
^12^ and for consultation rate, calculated by dividing the total number of clinic visits prior to the index date by the length of each patient's follow-up. If there are missing data in the covariates, we will consider using multiple imputation. Unfortunately not all covariates of interest, such as exercise, are recorded within the CPRD, and this may lead to unmeasured confounding. We hope to minimise this confounding by using methods, such as instrumental variable analysis, which can account for it to some degree.

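### In cohort A, a consultation rate fixed before the index date can reduce only baseline differences in practice contact, so the plan should not say that it overcomes ascertainment bias

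*Protocol article*

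**What the plan says.** The Bias section lists ascertainment bias first among three main sources of bias. It gives the mechanism: people with more chronic conditions "may have higher rates of consultation, which may also increase the opportunity for recording other diagnoses such as dementia". The remedy follows from that: "To overcome ascertainment bias, we will control for consultation rate in our analyses".

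Two other statements fix what this covariate can contain. In the same section, "we will define each covariate using data inputted prior to the index date". In the Covariates section, the rate is "calculated by dividing the total number of clinic visits prior to the index date" by a length of time. The reason for the timing rule is also given: "Collider bias could occur if we conditioned on events that happened as a result of the prescription the patient was issued".

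On the cohort A timeline, the text after Figure 1 says "Follow-up for cohort A will start on the first date a patient is diagnosed with the condition the treatment is used for or" (the sentence then names the at-risk date as the alternative). Table 1 puts the at-risk date first and uses the diagnosis date only when there was no at-risk period. The exposed are those who "received a treatment of interest within 6 months of initial diagnosis of the condition for which the treatment is being given", and everyone else in the cohort is unexposed (Cohort A). Under Outcomes, incident disease is identified from the earliest relevant Read code or product code in the practice record.

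**The concern.** The covariate and the bias it is meant to remove sit on different sides of the index date. For a patient who enters cohort A at risk, three things follow index: the diagnosis of the chronic condition, its treatment, and any contact with the practice that these bring. A rate measured before index contains none of them.

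The outcome depends on contact, because a dementia case counts only once it is coded. If exposed patients attend more after index, the recorded rate in that group may rise or the recording may come sooner, with no effect of the drug on disease. The cohort A incidence HR would then be biased upward, against the protective effect that the study is looking for. A reader told that this bias had been overcome would not allow for it.

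**Working it through.** **1. Timeline.** The plan's statements, side by side:

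| Element | Timing relative to index in cohort A | Source |
|---|---|---|
| Consultation rate (visits counted) | Before | Covariates; Bias |
| Entry at risk, or at diagnosis if no at-risk period | At index | Table 1; Cohort A |
| Diagnosis of the indication, for those entering at risk | After | Table 2; Cohort A |
| Treatment defining exposure | Usually after; at index for patients who enter on a treatment code | Cohort A; Table 2 |
| Contact that follows from treatment | After | Follows from the rows above |
| Recording of the outcome | After | Outcomes |

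The protocol does not give the share entering at risk. The bands in Table 2 are wide for blood pressure (systolic 120 to 139 mm Hg) and cholesterol (total 4 to 5 mmol/L). At risk of type 2 diabetes rests on a medical code alone.

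**2. Other planned steps.** The adjusted Cox and propensity analyses use the same covariates. The named inputs to the marginal structural weights include no consultation variable. Contact caused by treatment lies on the path from treatment to recording and is not a confounder, so methods for confounding, including the instrumental variable, do not remove it. The sensitivity analyses announced under Strengths and limitations concern the accuracy of dementia codes.

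**3. Size under assumed detection.** The plan states no figure to reproduce. If a constant share of cases is ever recorded in each group and the outcome is uncommon, then approximately

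HR observed = HR true × (detection in exposed ÷ detection in unexposed).

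The detection values are assumptions:

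- 0.65 ÷ 0.60 = 1.08. A true HR of 1 appears as 1.08, and 0.80 × 1.083 = 0.87.
- 0.70 ÷ 0.60 = 1.17. A true HR of 1 appears as 1.17, and 0.80 × 1.167 = 0.93.

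**4. Size if recording is only delayed.** One Cox simulation was run per row with 200,000 patients and a true HR of 1. All inputs are assumptions: a mean of 4 visits a year before index, treatment more likely in frequent attenders, onset at 0.015 a year, and a recording delay whose rate is 0.1 times the current yearly visits.

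| Extra visits a year in the exposed | Crude HR | HR adjusted for true pre-index rate (95% CI) |
|---|---|---|
| 0 | 1.07 | 1.00 (0.97 to 1.03) |
| 0.5 | 1.11 | 1.05 (1.01 to 1.08) |
| 1 | 1.13 | 1.06 (1.03 to 1.10) |
| 2 | 1.22 | 1.15 (1.11 to 1.19) |
| 4 | 1.25 | 1.19 (1.15 to 1.23) |

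The first row shows that the covariate does what it can: baseline ascertainment bias goes. The other rows show that the post-index part stays. The extra visits start at index in this simulation, which overstates the effect for patients treated much later.

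**5. Scale.** Table 3 gives no detectable HR for cohort A. The smallest elsewhere is 0.968 (cohort B, hypertension). A relative excess in recording of 1 ÷ 0.968 = 1.033, or 3.3%, would cancel an effect of that size.

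**The case against.** The best defence is that the Bias section describes patients who already have more chronic conditions. That is largely a prior difference, and a baseline rate is the right tool for it; the first row of the simulation agrees. The pre-index rule is also deliberate, since it avoids conditioning on consequences of the prescription. Both points stand. They show that the covariate is well chosen for baseline differences, not that it overcomes the bias in cohort A, where for at-risk entrants the named chronic condition itself appears after index.

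The contrast between groups is also weaker than treated against unmonitored. The unexposed include diagnosed but untreated patients and patients treated more than six months after diagnosis, while exposed patients who stop remain exposed. Some patients enter at diagnosis or on a treatment code. Dilution reduces the size. Entry at diagnosis or treatment does not remove the problem, because contact due to treatment still falls after index.

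Several stronger readings are tempting, and the documents do not support them:

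- **Recording rises with time on drug, or differs throughout follow-up.** No contact rates by group or over time are given. If monitoring mainly brings diagnosis forward, the excess could be early and fade, so a lag period cannot be dismissed as useless.
- **A protective effect will be hidden or reversed.** Reversing a true 0.80 needs a detection ratio above 1 ÷ 0.80 = 1.25, for example 0.65 against 0.50, which gives 1.04. Nothing in the protocol points to such a gap.
- **Cohort B should outweigh cohort A.** Cohort B compares subclasses among treated patients and is likely to be less affected, but it answers a different question and cannot settle a treated-against-untreated result.

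The Covariates section also divides the pre-index visits by length of follow-up, which conflicts with the pre-index rule unless prior recorded history is meant. That is a separate fault. The argument here holds even for a rate computed wholly before index.

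**Conclusion.** The concern holds in a limited form. The Bias section claims a property that the covariate does not have in cohort A: it can reduce baseline differences in contact but cannot remove differential recording that arises after index. The direction is upward if exposed patients are seen more often, which is plausible but not stated in the protocol.

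The size is unknown. Under the assumed detection values a true HR of 0.80 would appear as 0.87 to 0.93, which is attenuated but still protective. If recording is only delayed, the assumed 0.5 to 1 extra visit a year gives an HR of about 1.05 to 1.06 under no effect, and dilution would lower this further. Even so, a bias of a few per cent matters in a study that claims power for small effects. Cohort C is not affected in this way, since its outcome is death from linked national records.

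**What to change.** In the Bias section, change the claim from overcoming ascertainment bias to reducing baseline differences in it, and state that surveillance bias arising after index may remain in cohort A. Keep the pre-index rule and do not adjust for post-index consultations, in keeping with the plan's own collider argument.

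For cohort A, add three checks:

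1. Report post-index consultation rates by exposure group, for description only.
2. Run the same Cox and propensity models on a negative-control outcome, named in advance: a condition recorded at routine contacts that the drugs are not expected to affect.
3. Add a sensitivity analysis with a lag period from the index date, applied alike to both groups. It addresses an early excess only; for patients treated long after an at-risk entry it may remove little.

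Interpret the cohort A incidence HRs against these results. The cost is one extra outcome code list and repeat runs of models already planned. The drawback is that cohort A conclusions will be stated more cautiously.
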